## Abstract

**Background:**

In Cameroon, the coverage, completeness, and timeliness of the Expanded Programme on Immunization (EPI) vaccines administration in children have remained heterogeneous and below the national and districts targets in several districts. In an effort to solve this problem, many interventions have been tested but none has shown significant improvement of the situation.

**Objective:**

This trial aims to test whether involving Community Volunteers to assess children vaccination status and demographic movements and using recorded data to plan catch-up immunization sessions can improve children vaccination timeliness, completeness and coverage.

**Methods:**

Communities of the Foumban Health district, West region of Cameroon will be selected and assigned to either intervention or control groups using a restricted randomization of 2. In the intervention group, one Community Volunteer per community will be trained to visit households and record EPI-targeted children in a register, record their demographic movements, and assess their immunization status monthly for a year. The information recorded will be snapped and sent to the competent health center immunization team through WhatsApp. These will be used to plan and implement monthly community catch up immunization sessions in collaboration with the community volunteer. In the control group, the routine immunization sessions will be conducted with health centers organizing either weekly vaccination sessions for communities situated not farther than 5 kilometers away from the health facility or monthly vaccination sessions in communities situated more than 5 kilometers away from the health center. Baseline, mid-term and end-line surveys will be conducted to assess and compare immunization coverage, timeliness, and completeness.

**Results:**

Funded in 2018, data collection started in 2018 and has been completed. Data analysis and reporting are ongoing.

**Conclusions:**

This trial is expecting to test an innovative approach to improving children’s immunization timeliness, completeness and coverage of immunization by tracking EPI targeted population vaccination status and denominator at household level and building collaboration between the community and health facilities vaccination teams to organize monthly community-based response vaccination sessions. This intervention is expected to improve children sustainable access to EPI vaccination as it offers assessing and responding to their immunization needs at monthly basis using low cost local human resources.

**Trial Registration:**

Pan African Clinical Trials Registry ID PACTR201808527428720; tinyurl.com/u058qnse

**International Registered Report Identifier (IRRID):**

DERR1-10.2196/21734

## Introduction

Vaccines save lives cheaply, and many countries have adopted a number of antigens to be administered to children and pregnant women under the Expanded Programme on Immunization (EPI). The program has been successfully implemented in many contexts but in many others, vaccination performance in terms of coverage, completeness, and timeliness remains low and is associated with outbreaks of vaccine preventable diseases [1-3].

In Cameroon, 11 vaccines are planned to be administered to children and pregnant women through the EPI [4]. These vaccines are routinely offered in health facilities on a scheduled day weekly and monthly in communities with limited access to health care. Community-based sessions are outreach activities organized by health facility staff in collaboration with community volunteers. Due to limited resources (human, financial, vaccine supply and cold chain, transportation, and power supply) on one hand and limited knowledge of caregivers and their demographic movements on the other, many children fail to receive their planned vaccine doses, be vaccinated on time, or complete their vaccination as required by the national EPI program [1,5].

In 2018, the Demographic Health Survey conducted at the household (HH) level reported 86.7%, 71.5%, and 65.3% rates of vaccination for bacille Calmette-Guérin (BCG), Diphtheria-Pertussis-Tetanus and Hepatitis B + Hemophilus Influenzae type b (DPT-Hi+Hb3), and measles, respectively, with a zero-dose proportion of 9.7% [6]. Many other studies and reports highlighted heterogeneous immunization coverages and high dropout rates in the child vaccination cascade [7,8]. The association between missing planned vaccination doses and the incidence of EPI-preventable diseases is yet to be investigated in Cameroon. In other settings, low vaccination coverage, timeliness, and completeness rates have been consistently reported to be associated with a high incidence of EPI vaccine–preventable diseases (EPI-PD) [9]. Most cited factors associated with low immunization coverage and incomplete vaccination status of children include maternal socioeconomic status, forgetting the vaccination schedule, limited access to health care services, population health care–seeking behaviors, perception of vaccination, misestimating the targeted population, migration, and demographic movement [10].

Strategies have been tested in many countries to reduce missed opportunities of vaccination and improve access to vaccines. Those frequently reported to have shown some positive impact include providing information on immunization to parents and community members, offering memory cards specifically designed for immunization, offering vaccines through proximity vaccination sessions with or without incentives, identifying unvaccinated children in home visits and referrals to health facilities, and integration of immunization services with other services [11,12].

From previous experience with EPI activity supervision, we noticed that many children and pregnant women miss vaccinations during the scheduled periods because of short- or long-term travel. In the national immunization guidelines, no procedure has been planned to catch-up and reduce the time gaps between the recommended vaccination date and the date of vaccine administration. In about one-third of 191 currently functional health districts, most deliveries occur in communities, and newborns are not brought to health facilities to be vaccinated and thus not considered when planning outreach vaccination sessions. In the same line, immigrants and emigrants are not taken into account when planning or monitoring health facility or outreach immunization sessions. Nomads move permanently from one village to another and are not targeted by immunization sessions. In some cases, nomads’ children receive several doses of the same vaccine at any time on their way, but none is recorded. This often leads to delaying or not vaccinating about 30%-70% of the targeted EPI population depending on the district. In 2004, we were able to improve the rates of timely immunizations of the third dose of the combined DPT-Hi+Hb vaccine in the Mada Health District in Far North-Cameroon. This was done in a year, using community volunteers to record the following information at the community level: births, travel of the EPI-targeted population, and immunization status of immigrant children. The resulting information was communicated to the vaccinating health facility to plan immunization sessions and organize the catch-up of those who missed the sessions. There was neither a control group nor sufficient power to draw a conclusion from this experience. To the best of our knowledge, this has not yet been tested. This project aims to test if using community volunteers to record vaccination status and demographic movement of children at the HH level and using the recorded data to plan immunization sessions and organize catch-up of missing children can improve EPI immunization timeliness, completeness, and coverage.

## Methods

### Trial Status

The process of the field phase of the trial, which is ongoing, is described in Figure 1. The unique version of the protocol is registered in the Pan African Clinical Trials Registry with the number PACTR201808527428720. This protocol was also submitted to the Cameroon National Ethics committee for Human Health Research for ethical review, and after evaluation, ethical clearance (2018/07/1058/CE/CNERSH/SP) was obtained.

**Figure 1 figure1:**
[figure not shown]
CONSORT diagram of the study.

### Trial Design

This is a cluster randomized controlled trial in which communities of the targeted health district were randomly assigned to either the intervention or the control group. In the intervention group, community volunteers were trained to visit HHs monthly to record children’s immunization status and demographic movement in a community register, and the page of the register was scanned and sent to the health facility in charge of vaccination. The health facility vaccination team used the scanned page to plan where an outreach vaccination session was needed in the community. For the control group, EPI vaccination was organized as per routine, meaning on a weekly basis at health facilities for children living <5 km from the health facility or on a monthly basis during an outreach activity in the community for children situated ≥5 km away from the health facility.

### Study Site

The study was conducted in the Foumban Health District, West region of Cameroon, as shown in Figure 2. From the 2018 health population denominators of Cameroon, the total population of the district in 2018 was estimated at 235,828 inhabitants distributed in 311 communities [13]. This district is inhabited by a seminomadic population moving periodically each year with part or all their HH and cattle in search of pasture for farming activities. From weekly reports of the Epidemiological Surveillance Unit of the Department of Diseases Control, Cameroon Ministry of Public Health, it is one of the health districts that have been affected with at least one outbreak of EPI-PD during each of the previous 5 years.

**Figure 2 figure2:**
[figure not shown]
Map of the Foumban Health District.

### Study Period

This study was planned for a period of 18 months (from May 2018 to October 2019).

### Sampling

#### Sampling and Randomization of Clusters

To be eligible, communities had to have limited access to a vaccinating health facility and either have recorded a case of EPI-PD in the previous 12 months or belong to a health area with administrative DPT-Hi+Hb3 vaccine coverage <70% in the routinely EPI-targeted population. Communities with limited seasonal accessibility limiting the monitoring of the intervention in some period of the implementation of the intervention were excluded.

In this study, we considered a “community” to be the smallest geographic area (quarter) with a traditional leader (commonly called head of quarter) gathering 100-300 HHs in rural areas or 200-500 HHs in urban areas.

Selected communities were stratified according to their setting (urban/rural), the importance of yearly population movement, the distance to the vaccinating health facility, and the occurrence of EPI-PD in the previous year. In each stratum, communities were ranked in alphabetic order from A to Z and in blocks of 2. All combinations of blocks were listed, and a 1-digit number was assigned to each combination. Numbers were generated from Table XXXIII of Wishart [14], as follows: An arbitrary point was chosen in the table, and numbers were read in a single digit row by row across the page. Each number read and corresponding to a pair of communities dictated the distribution of these communities by study group. Randomized communities were divided into subunits of up to 200 buildings (ranging 100-150 HHs) called clusters using the Google Maps app installed on a smartphone. From previous experience, this is the number of buildings that can be visited in a week by a community volunteer to implement planned activities. One of these clusters per village was randomly chosen per village in each study group. To be able to compare immunization coverage and other indicators between baseline, midline, and endline surveys, eligible but not selected communities were similarly and independently randomized but did not receive the intervention.

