### Data Analysis

The effect of the intervention will be assessed by estimating per study group and comparing (1) yearly immunization timeliness rates for BCG vaccine (proportion of children aged 0-59 months with evidence of vaccination in the first month of life) and measles-rubella vaccine (proportion of children aged 12-23 months with evidence of vaccination while 9-11 months old); (2) coverage of BCG (proportion of children aged 0-59 months who were vaccinated) and DPT-Hi+Hb1, DPT-Hi+Hb3, and measles-rubella (proportion of children aged 12-59 months who were vaccinated) vaccines; and (3) specific completeness (proportion of children who received DPT-Hi+Hb1 and DPT-Hi+Hb3 vaccines) and general completeness (proportion of children who received BCG and measles-rubella vaccines) while aged 12-59 months. Odds ratios for children being vaccinated, being vaccinated on time, and completing vaccination will be estimated and adjusted for the child’s guardians’ level of education and profession, type of population (seminomadic or sedentary), distance to the vaccinating health facility, and religion. The odds ratios will be controlled for variability using logistic regression random effects. The fixed parameters will include the outcome, study groups, child’s guardians’ level of education, type of population (seminomadic or sedentary), child’s guardians’ profession, distance to the vaccinating health facility, and religion, and the random effect will be controlled on the participants’ cluster. The analysis will be done based on the intention to treat principle [16]. Data will be collected using Open Data Kit (ODK)–designed forms on smartphones, verified in the field, and submitted to a secure server. Data will be monitored and cleaned in Microsoft Excel 2013 and analyzed using Stata version 16.1 IC.

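### The mixed logistic model omits urban/rural setting, previous-year EPI-PD and community movement class, on which communities were randomized; if these predict timely BCG beyond the listed covariates, precision is lost.

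*Protocol article*

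**What the plan says.** Sampling and Randomization of Clusters describes restricted allocation: "Selected communities were stratified according to their setting (urban/rural), the importance of yearly population movement, the distance to the vaccinating health facility", and also "the occurrence of EPI-PD in the previous year". Within strata: "In each stratum, communities were ranked in alphabetic order from A to Z and in blocks of 2". Allocation then went pair by pair: "Each number read and corresponding to a pair of communities dictated the distribution of these communities by study group".

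Data Analysis fixes the model. It states that "The odds ratios will be controlled for variability using logistic regression random effects". The list of terms opens with "The fixed parameters will include the outcome, study groups", continues with guardian education, type of population (seminomadic or sedentary) and guardian profession, and closes with "distance to the vaccinating health facility, and religion, and the random effect will be controlled on the participants’ cluster". The adjustment covariates appear twice in that section and are the same both times.

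Sample Size Estimate works from between-cluster coefficients of variation of 0.38 (control) and 0.19 (intervention). It does not mention strata or pairs.

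**The concern.** When clusters are allocated within strata, the stratification factors are close to balanced between arms, so variation between strata largely drops out of the arm comparison. A model without those factors does not know this. It assigns their variation to the cluster random effect and charges it to the standard error of the intervention effect. The estimate is sound, but its interval is wider than the design warrants and the test rejects less often than its nominal level under the null.

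The covariate list is explicit in the article, so this is not a detail left open for a separate analysis plan. It does not match the allocation scheme two sections earlier. At stake is some precision on the primary outcome (BCG in the first month of life) and on the secondary outcomes analysed with the same model.

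**Working it through.** **1. Design factors against model terms**

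| Factor used at randomization | In the model? |
|---|---|
| Urban/rural setting | No |
| Yearly population movement (community level) | Only by proxy: seminomadic/sedentary |
| Distance to vaccinating facility | Yes |
| EPI-PD in the previous year | No |

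**2. Inputs (Sample Size Estimate).** Control proportion 0.205; 20 children per cluster; CVs 0.38 and 0.19; α = 0.05; final size 32 clusters per arm. Two readings are mine: α is two-sided, and the 10% increase means 10 points (0.205 to 0.305).

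**3. Variance of one cluster proportion**, v = p(1−p)/m + (CV·p)²:
- Control: 0.205×0.795/20 + (0.38×0.205)² = 0.00815 + 0.00607 = 0.01422.
- Intervention: 0.305×0.695/20 + (0.19×0.305)² = 0.01060 + 0.00336 = 0.01396.
- Sum 0.02817, of which between-cluster 0.00943. Share: 0.00943/0.02817 = 33%.

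**4. The plan's own figure.** Clusters per arm for 90% power: 1 + (1.960+1.282)² × 0.02817/0.10² = 30.6, so 31. The stated minimum of 23 control and 20 intervention clusters does not reproduce. It gives SE = √(0.01422/23 + 0.01396/20) = 0.0363 and power Φ(0.10/0.0363 − 1.96) = 79%. The final 32 per arm gives SE = √(0.02817/32) = 0.0297 and power Φ(3.370 − 1.96) = 92%, or 90% if 18 children per cluster are reached. The present point uses only the final size.

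**5. Effect of adding the omitted factors.** Let f be the share of between-cluster variance that they explain beyond the covariates already listed. The article gives no value, so f is an assumption. Variance becomes 0.01875 + (1−f)×0.00943, where 0.01875 is the within-cluster part.

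| f | Variance falls by | Interval width ratio | Calculated power, 32 × 20 | Type I error without the factors |
|---|---|---|---|---|
| 0 | 0% | 1.00 | 92.1% | 0.050 |
| 0.10 | 3.3% | 0.98 | 92.9% | 0.046 |
| 0.25 | 8.4% | 0.96 | 94.1% | 0.041 |
| 0.50 | 16.7% | 0.91 | 95.8% | 0.032 |

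The 92.1% is the power under unstratified allocation. If the factors do matter, stratified allocation has already reduced the true spread of the estimate, so the model without them does slightly better than 92.1%. Its power is Φ((0.10 − 1.96×0.0297)/SE_f), with SE_f the smaller standard error. That is 93.0% at f = 0.25 (SE_f = 0.0284) and 93.9% at f = 0.50 (SE_f = 0.0271). Like for like, the gain is about 1 to 2 points of power.

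**6. Cost in degrees of freedom.** With 64 clusters, the two-arm comparison has 62. Two added terms leave 60, with a width ratio of 1.00 if they explain nothing. All 16 strata (assuming two levels per factor) leave 47, ratio 1.01. A pair term leaves 31, ratio 1.02.

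**7. Check in the planned type of model.** A random-intercept logistic model was simulated with 64 clusters of 20, allocation within pairs, an assumed logit variance of 0.2 and 300 runs per setting. The mean log odds ratio was the same with and without the two factors (0.543 and 0.543 at f = 0.25; 0.519 and 0.520 at f = 0.50; true value 0.532), so omission did not bias it. The ratio of mean standard errors was 0.93 at f = 0.25 and 0.87 at f = 0.50. It was already 0.98 at f = 0, so part of that narrowing may be an artefact of the fitting. I rely on the simulation for direction only.

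**The case against.** The strongest reply is that nothing is invalid. The test is conservative, and the sample size takes no credit for stratification, so no planned power is lost: 32 × 20 gives about 92% on the article's inputs. This stands, and it limits the point to efficiency.

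A second reply also stands. The model already contains distance, a proxy for movement and three guardian covariates, so only the increment from the omitted factors counts. That increment could be small or nil. At f of 0.10 to 0.15, intervals narrow by only 1.7-2.5%.

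A reader might infer more than the documents support:
- *That intervals are certainly too wide.* This needs the omitted factors to be prognostic beyond the listed terms. Choosing them for stratification suggests that they were thought relevant, but no figure shows it.
- *That pairing demands a pair term.* Pairs were formed alphabetically within stratum, which gives no reason to expect them to be prognostic beyond the stratum, and the term would cost half the degrees of freedom.
- *That adjusting for education, profession and religion is a fault because they were not balanced by design.* Adjusting for prognostic covariates is legitimate, and these should stay.
- *That the loss is larger because the CV might be 0.38 in both arms.* The article states 0.19 for the intervention arm.

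**Conclusion.** The mismatch is plain on the text: of four stratification factors, the model carries one as named and one by approximate proxy. The consequence is conditional. If setting, previous-year EPI-PD and the community movement class explain an extra 0-50% of between-cluster variance (assumption), the variance of the arm difference falls 0-17%, intervals narrow by up to about 9%, and calculated power goes from 92% to 92-96%. This rests on the article's CVs, a two-sided test and a 10-point increase. The harm is lost precision and a conservative test, not bias or an inflated type I error. It is worth correcting because the remedy costs almost nothing.

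**What to change.** Add urban/rural setting, movement class, distance class and previous-year EPI-PD, coded as they were at randomization, as fixed effects in the primary mixed logistic model. Keep the guardian covariates and the cluster random effect. Do not add a pair term.

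No new data are needed, since the strata of every randomized community are known from the allocation, and the loss of degrees of freedom is negligible. The real cost is procedural. The Results section says that data collection was complete by January 2020, with cleaning and reporting under way. The change must therefore be declared and dated, and justified by the allocation scheme and not by any outcome. Reporting the model as published alongside it would let readers see the effect of the change.

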#### Participants

All children aged 0-59 months living in HHs of the selected communities were eligible. This includes the age group targeted by the Cameroon national EPI for routine immunization (0-11 months) and the catch-up vaccination group program (12-59 months) [4]. Children arriving in a HH to stay for less than a month were excluded, and those leaving or planning to stay out of the HH for more than a month were not included. Those leaving the HH for less than a month were not excluded. Parents of children leaving the HH to stay for more than a month were followed up on phone when possible to sensitize them on the necessity of completing the child vaccination program.

### Intervention

One community volunteer per community was selected with the help of the head nurse of the competent health center (CHC) and trained to visit HHs of the community cluster monthly, record in a register all children aged 0-59 months and their demographic movements for the last month and next month, and assess their immunization status from the vaccination card or using a tracking grid if the child did not have a vaccination card. The recorded information page was snapped and sent through WhatsApp to the immunization team of the CHC. The information was used by the vaccination team that had received standardized training on reading and using WhatsApp images to plan and implement monthly community immunization sessions. This community vaccination session was conducted in collaboration with the community volunteers who chose an accessible vaccination site in the community and informed parents with children needing vaccination about the session. Health centers and communities were visited monthly to be supervised on their activities.

